**OBJECTIVES, AIMS AND RATIONALE**

There are two main objectives of this study:

1. To refine the mother baby link, evaluating the opportunities brought by linked HES and ONS data.
2. To extend the mother baby link to a full pregnancy register including pregnancies resulting in termination, miscarriage and stillbirth.

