**EXPOSURES, OUTCOMES AND COVARIATES**

Pregnancy and pregnancy outcomes will be identified using the methods listed above. All women with at least one indication of pregnancy will be included in the pregnancy register. A Read code list of the existing codes for live birth is included as an appendix.

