**DISSEMINATION OF RESULTS**

The results of this study will be communicated to GPRD users and license holders. Findings will also be published for peer review in international scientific journals and conferences as appropriate.

It should be noted that all delivery dates will be estimated based upon probabilistic linkage, and GPRD will never release information as to whether a delivery date is a confirmed date of birth or not.

READ CODES FOR LIVE BIRTHS

| Read Code | Read Term |
| --- | --- |
| 6311 | Home birth |
| 6312 | GP unit birth |
| 6313 | Consultant unit birth |
| 6314 | Nursing home birth |
| 6315 | Ambulance birth |
| 6316 | Born before arrival |
| 6321 | 1st stage of labour length |
| 6322 | 2nd stage of labour length |
| 6323 | 3rd stage of labour length |
| 6331 | Single live birth |
| 6333 | Twins - both live born |
| 6334 | Twins - 1 still + 1 live born |
| 6335 | Twins - both still born |
| 6336 | Triplets - all live born |
| 6337 | Triplets -2 live+ 1 still born |
| 6341 | Baby male |
| 6342 | Baby female |
| 6343 | 2 male babies |
| 6344 | 2 female babies |
| 6345 | 1 male + 1 female baby |
| 6346 | 3 male babies |
| 6347 | 2 male + 1 female babies |
| 6348 | 1 male + 2 female babies |
| 6349 | 3 female babies |
| 6351 | Baby premature 36-38 weeks |
| 6352 | Baby v. premature 32-36 weeks |
| 6353 | Baby extremely prem.28-32 week |
| 6354 | Baby full term maturity |
| 6355 | Baby post-mature |
| 6356 | Baby premature 26-28 weeks |
| 6357 | Baby premature 24-26 weeks |
| 6358 | Baby premature 39 weeks |
| 6359 | Baby premature 38 weeks |
| 6361 | Baby BW = < 3% (under 2500g) |
| 6362 | Baby BW = 3% - 9% (2500-2849g) |
| 6363 | Baby BW = 10%-24% (2850-3149g) |
| 6364 | Baby BW = 25%-49% (3150-3449g) |
| 6365 | Baby BW = 50%-74% (3450-3749g) |
| 6366 | Baby BW = 75%-89% (3750-4049g) |
| 6367 | Baby BW = 90%-96% (4050-4399g) |
| 6368 | Baby BW = > 96% (over 4499g) |
| 6369 | Baby BW = 4400 - 4499g |
| 6371 | Birth HC = < 3rd centile |
| 6372 | Birth HC = 3rd-9th centile |
| 6373 | Birth HC = 10th-24th centile |
| 6374 | Birth HC = 25th-49th centile |
| 6375 | Birth HC = 50th-74th centile |
| 6376 | Birth HC = 75th-89th centile |
| 6377 | Birth HC = 90th-96th centile |
| 6378 | Birth HC = > 97th centile |
| 6381 | Birth length = < 3rd centile |
| 6382 | Birth length=3rd-9th centile |
| 6383 | Birth length=10th-24th centile |
| 6384 | Birth length=25th-49th centile |
| 6385 | Birth length=50th-74th centile |

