| L246200 | Other cervical abnormality - baby delivered+postpartum compl |
| L246211 | Polyp of cervix - baby delivered+postpartum complication |
| L246411 | Polyp of cervix complicating p/n care - baby deliv prev |
| L247111 | Septate vagina - baby delivered |
| L24z400 | Pelvic soft tissue abnorm in preg/childb/puerp with p/n comp |
| L250100 | Fetus with central nervous system malformation - delivered |
| L251100 | Fetus with chromosomal abnormality - delivered |
| L252100 | Fetus with hereditary disease - delivered |
| L255100 | Fetus with drug damage - delivered |
| L25y100 | Fetus with other damage NEC - delivered |
| L25z100 | Fetus with damage NOS - delivered |
| L261100 | Rhesus isoimmunisation - delivered |
| L262100 | Other blood-group isoimmunisation - delivered |
| L263100 | Fetal distress - delivered |
| L263300 | Labour and delivery complicated by fetal heart rate anomaly |
| L263400 | Labour and delivery complic by meconium in amniotic fluid |
| L263500 | Lab+del comp fetal ht rate anom wth meconium in amnio fluid |
| L263600 | Labour+delivery complicatd by biochem evidence/fetal stress |
| L264100 | Intrauterine death - delivered |
| L265100 | Small-for-dates - delivered |
| L266100 | Large-for-dates - delivered |
| L270100 | Polyhydramnios - delivered |
| L280100 | Oligohydramnios - delivered |
| L281100 | Premature rupture of membranes - delivered |
| L281300 | Prem rupture of membranes onset of labour within 24 hours |
| L281400 | Premature rupture of membranes, labour delayed by therapy |
| L281500 | Prem rupture of membranes onset of labour after 24 hours |
| L282100 | Prolonged spont/unspec rupture of membranes - delivered |
| L284100 | Amniotic cavity infection - delivered |
| L28y100 | Other problem of amniotic cavity and membranes - delivered |
| L29..00 | Other problems affecting labour |
| L290.00 | Failed mechanical induction |
| L290.11 | Failed mechanical induction of labour |
| L291.00 | Failed medical or unspecified induction |
| L291.11 | Failed medical induction of labour |
| L291100 | Failed medical or unspecified induction - delivered |
| L291z00 | Failed medical or unspecified induction NOS |
| L292.00 | Maternal pyrexia during labour, unspecified |
| L292100 | Unspecified maternal pyrexia during labour - delivered |
| L293100 | Septicaemia during labour - delivered |
| L294.00 | Grand multiparity |
| L294000 | Grand multiparity unspecified |
| L294100 | Grand multiparity - delivered |

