| ZV24.00 | [V]Postpartum care and examination |
| ZV24.11 | [V]Postnatal care and examination |
| ZV24000 | [V]Examination immediately after delivery |
| ZV24100 | [V]Examination of Lactating mother |
| ZV24200 | [V]Routine postpartum follow-up |
| ZV24y00 | [V]Other specified postpartum care and examination |
| ZV24z00 | [V]Unspecified postpartum care and examination |
| ZV27.11 | [V]Live birth |
| ZV27000 | [V]Single live birth |
| ZV27200 | [V]Twins, both live born |
| ZV27300 | [V]Twins, one live born and one stillborn |
| ZV27500 | [V]Other multiple birth, all live born |
| ZV29.00 | [V]Level of neonatal care |
| ZV29.11 | [V] Level of care administered to neonates |
| ZV29000 | [V]Normal level of neonatal care |
| ZV29011 | [V] Normal care administered to neonates |
| ZV29100 | [V]Newborn receiving special care |
| ZV29111 | [V]Neonatal care in SCBU |
| ZV29200 | [V]Newborn receiving intensive care |
| ZV29211 | [V]Neonatal care on ITU |
| ZV29212 | [V]Neonatal care on NNU |
| ZV29300 | [V]Level 2 intensive care (high dep int care) admin neonate |
| ZV3..00 | [V]Healthy liveborn infants according to type of birth |
| ZV30.00 | [V]Singleton |
| ZV30000 | [V]Singleton, born in hospital |
| ZV30100 | [V]Singleton, born before admission to hospital |
| ZV30z00 | [V]Singleton NOS |
| ZV31.00 | [V]Twin, mate live born |
| ZV31000 | [V]Twin, born in hospital, mate live born |
| ZV31200 | [V]Twin, not hospitalised, mate live born |
| ZV31z00 | [V]Twin, mate liveborn, NOS |
| ZV32.00 | [V]Twin, mate stillborn |
| ZV32000 | [V]Twin, born in hospital, mate stillborn |
| ZV32z00 | [V]Twin, mate stillborn, NOS |
| ZV33.00 | [V]Twin, unspecified |
| ZV33000 | [V]Twin, unspecified, born in hospital |
| ZV33z00 | [V]Twin, unspecified, NOS |
| ZV36100 | [V]Other multiple birth, before hospital, mates live+still |
| ZV3yz00 | [V]Other multiple birth, unspecified, NOS |
| ZV3z.00 | [V]Unspecified birth |
| ZV3z000 | [V]Unspecified birth, born in hospital |
| ZV3zz00 | [V]Unspecified birth, NOS |

1. Entity types are record type identifiers within Vision that control the entry of specific clinical data such as birth details or antenatal visit information, and also control the way in which test results are recorded. [↑](#footnote-ref-2)

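### The Read code list for live births includes one code that rules out a live birth (6335) and one that records a fetal death (L264100), and nothing in the protocol overrides them

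*Protocol*

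**What the plan says.** The section on exposures, outcomes and covariates states: "A Read code list of the existing codes for live birth is included as an appendix". The appendix, printed after the dissemination section, carries the heading "READ CODES FOR LIVE BIRTHS". It is a two-column table of codes and terms, with no field for outcome, number of babies or role in the algorithm.

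Two entries conflict with that heading:

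- 6335: "Twins - both still born"
- L264100: "Intrauterine death - delivered"

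The second objective is "To extend the mother baby link to a full pregnancy register including pregnancies resulting in termination, miscarriage and stillbirth". Under Data Analysis, Stage Three takes up that extension only once the link has been optimised for mothers and live births. Stage Three also says that a way of handling conflicting records has still to be worked out.

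**The concern.** A list that identifies live births should not contain a term stating that no baby was born alive. The register is meant to hold pregnancy outcomes, and stillbirth is one of those it adds. If 6335 stays on the live-birth list, a delivery recorded only by that code enters the link as a live birth.

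Two harms could follow. The pregnancy outcome would be wrong. The delivery would also have no true surviving child, which leaves an opening for another child of the same family to be attached to it. The Background section gives research on teratogenic drug effects as a leading use. For that research, a fetal death filed as a live birth hides the adverse outcome, and a wrong link assigns the in-utero exposure to the wrong child.

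**Working it through.** The protocol states no figure on this point and gives no counts by code, so there is no arithmetic to reproduce. The check is a reading of the terms against the list's stated purpose.

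1. **Purpose of the list.** The heading and the sentence that introduces it agree that these are codes for live birth.

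2. **Terms incompatible with that purpose.** Code 6335 describes a twin delivery with no survivor, so it cannot coexist with a live birth from the same delivery. L264100 records a death in utero. In a singleton pregnancy it also excludes a live birth. In a multiple pregnancy it could be entered while a co-twin survives. 6335 is therefore the unarguable error, and L264100 is an error unless a live co-twin is recorded.

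3. **Terms that look similar but are correct.** Code 6334 ("Twins - 1 still + 1 live born") and code 6337 ("Triplets -2 live+ 1 still born") each state at least one live birth, and so does ZV27300. ZV32.. and ZV36100 come after the ZV3..00 heading for healthy liveborn infants, so they read as describing the liveborn child. The neonatal and infant death codes (Q48y600, Q48y700, Q4z..11 to Q4z..13) concern babies who died after birth. All of these belong on the list.

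4. **Any exclusion or override.** None is stated. The nearest text is the Stage Three remark on conflicting records. It comes after the live-birth link has been optimised. It also could not catch a delivery whose only record is 6335, because there is no second record to conflict with it.

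5. **Route from a wrong code to a wrong link.** Study Population admits as candidate children all acceptable registered patients born after 1986. Limitations says that matching is probabilistic, that date of birth is not available and that many babies lack a birth month. A delivery with no surviving child could therefore be matched to a sibling. This needs two conditions: the algorithm must accept a listed code as evidence of a live birth, and a plausible registered child must exist. The protocol confirms neither.

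6. **Whether later validation would find it.** Stage Four comes after all information has been incorporated. It searches free text for evidence of pregnancies and asks GPs whether mother-baby matches are correct. Nothing says that deliveries with stillbirth codes will be examined. A question about matches also cannot reveal a misclassified delivery that was never matched.

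**The case against.** The strongest reply is that the list may in practice serve as evidence of delivery, with the child's own registration showing that the baby lived. Much of the list fits that reading: length of labour, placental details, absence of postnatal care, older first-time mothers and maternal obstetric death say nothing about the baby's vital status. On this view the heading is loose, but a stillbirth code does not by itself create a live birth. The protocol also calls these the existing codes, which makes them a starting point, and its first objective is to refine the link.

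Part of this stands. The algorithm is not described, so the consequence is conditional. Taking out two codes would not make the list specific to live births. But a code that is silent on vital status differs from one that denies a live birth, and the protocol itself names the list as the one for live birth. None of the planned refinements mentions either code.

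A reader might also infer that the mixed-outcome codes are wrongly included. They are not, since each includes a live birth. Recording the stillborn sibling belongs to Stage Three, which is not yet specified.

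**Conclusion.** The contradiction is certain for 6335. For L264100 it holds unless a live-born co-twin is recorded. It is an error in a printed outcome code list, not a detail left for later specification. The consequence rests on one assumption, that a listed code is accepted as evidence of a live birth. Under it, a delivery identified only by 6335 has the wrong outcome, and a false link is possible but not assured.

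The size is unknown and may be small: two codes in a very long list, one of them confined to twin pairs with no survivor.

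Two stronger readings are not supported:

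- **That every delivery carrying either code is misclassified.** The algorithm is not given, other records may be present, and L264100 allows for a surviving co-twin.
- **That thousands of deliveries are at risk.** An assumed stillbirth share of 0.3% to 0.8% applied to the 886,677 babies in the March 2011 link gives 886,677 × 0.003 = 2,660 to 886,677 × 0.008 = 7,093. That figure has no bearing here. It uses an assumed rate for all stillbirths, not the frequency of these two codes, and its base is babies already linked, not deliveries.

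The point still deserves correction before the list is carried into the register, because the error is plain and cheap to remove.

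**What to change.** - Move 6335 from the live-birth list to a stillbirth and fetal-death list.
- Treat L264100 as a fetal death that overrides live-birth status before linkage, unless a live-born co-twin is recorded. Deleting it outright could lose true live births.
- Keep 6334, 6337, ZV27300, ZV32.. and ZV36100 on the live-birth list. Flagging them so that Stage Three can add the stillborn sibling is a useful option, not a correction.
- Re-run the existing link with these changes, and report how many deliveries change outcome and how many mother-baby links change. This supplies the count that the protocol lacks.

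The cost is a code-list edit and one re-run of a link that the Background section says is already produced monthly. No new data are needed.

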| 63B5.00 | Apgar at 10 minutes = 4 |
| 63B6.00 | Apgar at 10 minutes = 5 |
| 63B7.00 | Apgar at 10 minutes = 6 |
| 63B8.00 | Apgar at 10 minutes = 7 |
| 63B9.00 | Apgar at 10 minutes = 8 |
| 63BA.00 | Apgar at 10 minutes = 9 |
| 63BB.00 | Apgar at 10 minutes = 10 |
| 63BZ.00 | Apgar at 10 minutes NOS |
| 63C..00 | Baby misc. ""at-risk"" factors |
| 63C1.00 | Risk factor - been on SCBU |
| 63C1.11 | Risk factor - been on special care unit |
| 63C2.00 | Bonding problems |
| 63C3.00 | Cot death liability |
| 63C4.00 | Battered baby suspect - FH |
| 63C5.00 | Maternal tobacco abuse |
| 63C6.00 | Maternal drug abuse |
| 63C7.00 | Maternal alcohol abuse |
| 63C8.00 | Mother < 20 years old |
| 63C9.00 | Mother has a social worker |
| 63CA.00 | H.V.: mother not managing well |
| 63CB.00 | Risk of non-accidental injury |
| 63CC.00 | Difficult to establish feeding |
| 63CD.00 | High risk infant |
| 63CE.00 | One of twins |
| 63CE.11 | Fraternal twin |
| 63CE.12 | Heterozygous twin |
| 63CE.13 | Identical twin |
| 63CE.14 | Monozygous twin |
| 63CF.00 | One of triplets |
| 63CZ.00 | Baby ""at-risk"" factors NOS |
| 63D..00 | Placental details |
| 63D1.00 | Placental weight |
| 63D2.00 | Placenta normal O/E |
| 63D3.00 | Placenta diameter |
| 63D4.00 | Placental infarct |
| 63D5.00 | Placental abnormality |
| 63D6.00 | Placenta incomplete |
| 63DZ.00 | Placental details NOS |
| 63E..00 | Labour details |
| 63E1.00 | Spontaneous onset of labour |
| 63E2.00 | Normal birth |
| 63E3.00 | Normal labour |
| 63F..00 | Birth details not known |
| 63Z..00 | Birth details NOS |
| 63Z..11 | Apgar normal |
| 641..00 | Infant feeding - at 10 days |
| 641Z.00 | Infant feeding at 10 days NOS |
| 642..00 | Infant feeding at 6 weeks |
| 642Z.00 | Infant feeding at 6 weeks NOS |
| 643..00 | Infant feeding at 3 months |
| 643Z.00 | Infant feeding at 3 months NOS |
| 644..00 | Infant feeding at 6 months |
| 644Z.00 | Infant feeding at 6 months NOS |
| 64a..00 | Child 8 week exam |
| 64a1.00 | Child 8 week exam. not offered |
| 64a2.00 | Child 8 week exam. not wanted |
| 64a3.00 | Child 8 week exam.not attended |
| 64a4.00 | Child 8 week exam. normal |
| 64a5.00 | 8 week exam.abnormal -for obs. |
| 64a6.00 | 8 week exam.abnormal -referred |
| 64a7.00 | 8 week exam.abn.-on treatment |
| 64B..00 | Child exam. - birth |
| 64B1.00 | Child not examined at birth |
| 64B2.00 | Child birth exam. - normal |
| 64B2.11 | Baby normal at birth |
| 64B3.00 | Birth exam. abnormal -for obs. |

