| L180400 | Diabetes mellitus in pueperium - baby previously delivered |
| L181100 | Thyroid dysfunction during pregnancy - baby delivered |
| L181500 | Postpartum thyroiditis |
| L182100 | Anaemia during pregnancy - baby delivered |
| L182200 | Anaemia in the puerperium - baby delivered |
| L182400 | Anaemia in the puerperium - baby previously delivered |
| L183100 | Drug dependence during pregnancy - baby delivered |
| L184400 | Mental disorder in puerperium - baby previously delivered |
| L185100 | Congenital cardiovasc dis in pregnancy - baby delivered |
| L185400 | Congenital cardiovasc dis in puerp - baby previously deliv |
| L188100 | Abnormal GTT during pregnancy - baby delivered |
| L188200 | Abnormal GTT in puerperium - baby delivered |
| L18z100 | Medical condition NOS during pregnancy - baby delivered |
| L20..00 | Normal delivery in a completely normal case |
| L20..11 | Spontaneous vaginal delivery |
| L200.00 | Normal delivery but ante- or post- natal conditions present |
| L20z.00 | Normal delivery in completely normal case NOS |
| L210100 | Twin pregnancy - delivered |
| L211100 | Triplet pregnancy - delivered |
| L213.00 | Multiple delivery |
| L213000 | Multiple delivery, all spontaneous |
| L213100 | Multiple delivery, all by forceps and vacuum extractor |
| L213200 | Multiple delivery, all by caesarean section |
| L21z100 | Multiple pregnancy NOS - delivered |
| L22..11 | Malpresentation of fetus |
| L220100 | Unstable lie - delivered |
| L221100 | Cephalic version NOS - delivered |
| L222.00 | Breech presentation |
| L222.11 | Assisted breech delivery |
| L222.12 | Breech delivery |
| L222.13 | Spontaneous breech delivery |
| L222000 | Breech presentation unspecified |
| L222100 | Breech presentation - delivered |
| L222200 | Breech presentation with antenatal problem |
| L222z00 | Breech presentation NOS |
| L223.00 | Oblique presentation |
| L224.00 | Transverse presentation |
| L224100 | Transverse lie - delivered |
| L224z11 | Shoulder presentation |
| L225.00 | Face presentation |
| L225000 | Face presentation unspecified |
| L225100 | Face presentation - delivered |
| L225z00 | Face presentation NOS |
| L226.00 | Brow presentation |
| L226100 | Brow presentation - delivered |
| L226200 | Brow presentation with antenatal problem |
| L227.00 | High head at term |
| L227z00 | High head at term NOS |
| L228.00 | Multiple pregnancy with malpresentation |
| L229.00 | Prolapsed arm presentation |
| L22y.11 | Compound presentation |

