| L294z00 | Grand multiparity NOS |
| L295.00 | Elderly primigravida |
| L296.00 | Vaginal delivery following previous caesarean section |
| L29z.00 | Problems affecting labour NOS |
| L29zz00 | Problems affecting labour NOS |
| L3...00 | Complications occurring during labour and delivery |
| L30..00 | Obstructed labour |
| L300.00 | Obstructed labour due to fetal malposition |
| L300100 | Obstructed labour due to fetal malposition - delivered |
| L300300 | Obstructed labour due to breech presentation |
| L300400 | Obstructed labour due to face presentation |
| L300700 | Obstructed labour due to compound presentation |
| L301.00 | Obstructed labour caused by bony pelvis |
| L301400 | Obstructed labour due to generally contracted pelvis |
| L301500 | Obstructed labour due to pelvic inlet contraction |
| L302.00 | Obstructed labour caused by pelvic soft tissues |
| L302000 | Obstructed labour caused by pelvic soft tissues unspecified |
| L303.00 | Deep transverse arrest (DTA) |
| L303000 | Deep transverse arrest unspecified |
| L303100 | Deep transverse arrest - delivered |
| L303z00 | Deep transverse arrest NOS |
| L304.00 | Persistent occipitoposterior or occipitoanterior position |
| L304100 | Persistent occipitopost/occipitoant position - delivered |
| L305.00 | Shoulder dystocia |
| L305.11 | Impacted shoulders |
| L305000 | Shoulder dystocia unspecified |
| L305100 | Shoulder dystocia - delivered |
| L305200 | Shoulder dystocia with antenatal problem |
| L305z00 | Shoulder dystocia NOS |
| L306.00 | Locked twins |
| L306100 | Locked twins - delivered |
| L307.00 | Failed trial of labour unspecified |
| L307200 | Other failed trial of labour with antenatal problem |
| L307z00 | Failed trial of labour NOS |
| L308.00 | Failed forceps unspecified |
| L308100 | Other failed forceps - delivered |
| L308z00 | Failed forceps NOS |
| L309.00 | Failed ventouse extraction unspecified |
| L309000 | Other failed ventouse extraction, unspecified |
| L309100 | Other failed ventouse extraction - delivered |
| L309z00 | Failed ventouse extraction NOS |
| L30z.00 | Obstructed labour NOS |
| L30z000 | Obstructed labour NOS, unspecified |
| L30z100 | Obstructed labour NOS - delivered |
| L30zz00 | Obstructed labour NOS |
| L30zz11 | Dystocia NOS |
| L31..00 | Abnormal forces of labour |
| L310.00 | Primary uterine inertia |
| L311.00 | Secondary uterine inertia |
| L311200 | Secondary uterine inertia with antenatal problem |
| L312.00 | Other uterine inertia |

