| L371000 | Retained products with no haemorrhage unspecified |
| L371100 | Retained products with no haemorrhage - deliv with p/n prob |
| L371200 | Retained products with no haemorrhage with postnatal problem |
| L371z00 | Retained products with no haemorrhage NOS |
| L37z.00 | Retained placenta or membranes with no haemorrhage NOS |
| L38..00 | Complications of anaesthesia during labour and delivery |
| L380.00 | Obstetric anaesthesia with pulmonary complications |
| L380.11 | Mendelson's syndrome |
| L382000 | Obstetric anaesthesia with CNS complications unspecified |
| L383.00 | Obstetric toxic reaction to local anaesthesia |
| L384.00 | Obstetric spinal and epidural anaesthesia-induced headache |
| L384100 | Spinal/epidural anaesth-induced headache during puerp |
| L385.00 | Failed or difficult intubation during pregnancy |
| L386.00 | Toxic reaction to local anaesthesia during labour and deliv |
| L387.00 | Spinal/epidural anesth-induced headache dur labour/delivery |
| L388.00 | Cardiac comps of anaesthesia during labour and delivery |
| L389.00 | CNS comps of anaesthesia during labour and delivery |
| L38A.00 | Failed or difficult intubation during labour and delivery |
| L38B.00 | Failed or difficult intubation during the puerperium |
| L39..00 | Other complications of labour and delivery NEC |
| L390.00 | Maternal distress |
| L391.00 | Obstetric shock |
| L391000 | Obstetric shock unspecified |
| L392.00 | Maternal hypotension syndrome |
| L392000 | Maternal hypotension syndrome unspecified |
| L392z00 | Maternal hypotension syndrome NOS |
| L393.00 | Acute renal failure following labour and delivery |
| L393000 | Post-delivery acute renal failure unspecified |
| L393100 | Post-delivery acute renal failure - delivered with p/n prob |
| L393200 | Post-delivery acute renal failure with postnatal problem |
| L394.00 | Other complications of obstetric procedures |
| L394100 | Other complications of obstetric procedures - delivered |
| L394200 | Other complications of obstetric procedures - del +p/n prob |
| L394500 | Infection of obstetric surgical wound |
| L394600 | Haematoma of obstetric wound |
| L394z00 | Other complications of obstetric procedures NOS |
| L395.00 | Forceps delivery |
| L395.11 | Keilland's forceps delivery |
| L395.12 | Neville - Barnes forceps delivery |
| L395.13 | Simpson's forceps delivery |
| L395000 | Forceps delivery unspecified |
| L395100 | Forceps delivery - delivered |
| L395200 | Low forceps delivery |

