| L452000 | Obstetric nonpurulent mastitis unspecified |
| L452100 | Obstetric nonpurulent mastitis - delivered |
| L452200 | Obstetric nonpurulent mastitis - deliv with p/n complication |
| L452300 | Obstetric nonpurulent mastitis with antenatal complication |
| L452400 | Obstetric nonpurulent mastitis with postnatal complication |
| L452z00 | Obstetric nonpurulent mastitis NOS |
| L45y.00 | Other obstetric breast infections |
| L45y000 | Other obstetric breast infection unspecified |
| L45y100 | Other obstetric breast infection - delivered |
| L45z.00 | Obstetric breast infection NOS |
| L45z000 | Obstetric breast infection NOS, unspecified |
| L45z100 | Obstetric breast infection NOS - delivered |
| L45z400 | Obstetric breast infection NOS with postnatal complication |
| L45zz00 | Obstetric breast infection NOS |
| L46..00 | Obstetric breast and lactation disorders NOS |
| L46..11 | Lactation problems |
| L460.00 | Retracted nipple in pregnancy, the puerperium or lactation |
| L460000 | Retracted nipple in pregnancy/puerperium/lactation unspec |
| L460300 | Retracted nipple in pregnancy/puerperium/lact with a/n comp |
| L460z00 | Retracted nipple in pregnancy/puerperium/lactation NOS |
| L461.00 | Cracked nipple in pregnancy, the puerperium or lactation |
| L461.11 | Fissure of nipple |
| L461000 | Cracked nipple in pregnancy/puerperium/lactation unspecified |
| L461100 | Cracked nipple in pregnancy/puerperium/lactation - delivered |
| L461200 | Cracked nipple in pregnancy/puerp/lact - deliv + p/n comp |
| L461400 | Cracked nipple in pregnancy/puerperium/lactation + p/n comp |
| L461z00 | Cracked nipple in pregnancy, the puerperium or lactation NOS |
| L462.00 | Breast engorgement in pregnancy, the puerperium or lactation |
| L462000 | Breast engorgement in pregnancy/puerperium/lactation unspec |
| L462100 | Breast engorgement in pregnancy/puerperium/lactation - deliv |
| L462200 | Breast engorgement in pregnancy/puerp/lact - del + p/n comp |
| L462300 | Breast engorgement in pregnancy/puerperium/lact + a/n comp |
| L462400 | Breast engorgement in pregnancy/puerperium/lact + p/n comp |
| L462z00 | Breast engorgement in pregnancy/puerperium/lactation NOS |
| L462z11 | Breast engorgement |
| L463.00 | Other breast disorder in pregnancy/puerperium/lactation |
| L463000 | Other breast disorder in pregnancy/puerperium/lact unspec |
| L463300 | Other breast disorder in pregnancy/puerperium/lact +a/n comp |

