| Qyu3800 | [X]Other apnoea of newborn |
| Qyu3900 | [X]Other specified respiratory conditions of newborn |
| Qyu3A00 | [X]Oth cardiovascular disorders originating/perinatal period |
| Qyu4100 | [X]Sepsis/newborn due to other+unspecified staphylococcus |
| Qyu4200 | [X]Other bacterial sepsis of newborn |
| Qyu4800 | [X]Sepsis of newborn due to other+unspecified streptococci |
| Qyu5800 | [X]Neonat jaun due/drg,toxn transmit frm mother/given newbrn |
| Qyu5900 | [X]Neonatal jaundice due/other specifd excessive haemolysis |
| Qyu5A00 | [X]Neonatal jaundice from other+unspcf hepatocellular damage |
| Qyu5B00 | [X]Neonatal jaundice from other specified causes |
| Qyu5C00 | [X]Other congenital anaemias, not elsewhere classified |
| Qyu6000 | [X]Other neonatal hypoglycaemia |
| Qyu6C00 | [X]Transitory metabolic disturbance of newborn, unspecified |
| Qyu8000 | [X]Other hypothermia of newborn |
| Qyu8400 | [X]Hypothermia of newborn, unspecified |
| QyuA000 | [X]Oth specified disturbances of cerebral status of newborn |
| QyuA200 | [X]Other disorders of muscle tone of newborn |
| QyuA400 | [X]Disorder of muscle tone of newborn, unspecified |
| Z241.00 | Labour established |
| Z241100 | Onset of labour induced |
| Z243.00 | Observation of first stage of labour |
| Z243100 | First stage of labour established |
| Z243200 | First stage of labour not established |
| Z243300 | Progress of labour - first stage |
| Z243400 | Rapid first stage of labour |
| Z243411 | Rapid progress in first stage of labour |
| Z243500 | Normal length of first stage of labour |
| Z243600 | Slow progress in first stage of labour |
| Z243800 | First stage of labour problem |
| Z244100 | Observation of duration of labour |
| Z244300 | Short duration of labour |
| Z244400 | Late onset of labour |
| Z244411 | Postmature labour |
| Z244500 | Relation of onset of labour to due date |
| Z245.00 | Observation of blood loss in labour |
| Z245100 | Maternal blood loss minimal |
| Z245200 | Maternal blood loss within normal limits |
| Z245300 | Maternal blood loss moderate |
| Z245400 | Maternal blood loss heavy |
| Z246.00 | Observation of measures of labour |
| Z246100 | Duration of labour |
| Z246200 | Onset of labour first stage |
| Z246211 | Start of labour |
| Z246300 | Onset of contractions |
| Z246311 | Onset of labour pains |
| Z246400 | Time contractions became regular |
| Z246600 | Time rupture of membranes detected |
| Z246611 | Time waters ruptured |

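### The live-birth code list contains antenatal and pregnancy-status codes that do not show a birth, so pregnancies not known to have ended in a live birth can be classed as live births

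*Protocol*

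**What the plan says.** The Protocol section on exposures, outcomes and covariates states: "A Read code list of the existing codes for live birth is included as an appendix". The appendix is headed "READ CODES FOR LIVE BIRTHS". It is a single undivided table of codes and terms. Nothing in it says whether a code is looked for in the mother's or the child's record, or whether it proves a delivery or merely supports one.

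Among its entries are:
- "Breech presentation with antenatal problem" (L222200)
- "Breast engorgement in pregnancy/puerperium/lact + a/n comp" (L462300)
- "Elderly primigravida" (L295.00)
- "Failed or difficult intubation during pregnancy" (L385.00)
- "First stage of labour not established" (Z243200)
- "Identical twin" (63CE.13)

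The surrounding rules are brief. Any woman with one or more indications of pregnancy enters the pregnancy register (Exposures, Outcomes and Covariates). Delivery records are limited to mothers aged 12 to 49 at the estimated delivery date (Study Population). Both a delivery date for the mother and a birth date for the baby are estimated (Data Analysis, Stage One). Rules for conflicting records are still to be set (Stage Three). Validation comes after the register is built (Stage Four).

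**The concern.** A code list defines an outcome. If a list labelled live birth admits codes that are compatible with an ongoing pregnancy, the outcome it defines is not live birth.

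Two things are at stake. First, the second objective is a register that separates live births from terminations, miscarriages and stillbirths. A pregnancy coded antenatally and later lost can be put in the wrong outcome class. Second, the Background promotes the resource for studies that need information in all three trimesters. A delivery date drawn from an antenatal code can fall too early and carry the estimated conception date and exposure windows with it.

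Users would have little means of spotting this. The Dissemination section says they will never be told whether a delivery date is a confirmed date of birth.

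**Working it through.** The Protocol states no figure to reproduce on this point. The check is a hand read of the appendix against the rules in the body text.

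**1. Terms explicitly qualified as antenatal.** The count takes every term ending in an antenatal problem or complication, written out or abbreviated a/n:
- L222200, L226200, L237200
- L305200, L307200
- L311200, L312200
- L323200
- L33y200, L33z200
- L350200
- L440300, L452300
- L460300, L462300, L463300, L466300

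Total: 3 + 2 + 2 + 1 + 2 + 1 + 2 + 4 = 17. Two further terms mention an antenatal state but also state delivery (L413100 and L200.00). They are not counted.

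**2. How many have a delivered version on the same list?** L222100, L226100, L237100, L305100, L312100, L323100, L33z100, L440100, L452100, L462100 and L466100 are all listed. That is 11 of 17. For these conditions the list itself distinguishes the two states and still includes both.

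**3. How many of the 17 nonetheless point to labour or the puerperium?** L305200 (shoulder dystocia), L307200 (failed trial of labour), L311200 and L312200 (uterine inertia), L323200 (delayed second twin) and L440300 (puerperal cerebrovascular disorder). That is about 6, leaving 17 − 6 = 11 that do not. This is a different set of 11 from step 2. Four of the six (L305, L312, L323, L440) have a delivered version, so 11 − 4 = 7 of the remaining 11 have one too.

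**4. Pregnancy-status terms without an antenatal label.** L295.00, L294.00 (grand multiparity, with its delivered version L294100 also listed), L227.00 (high head at term), L385.00 and Z243200. None of these terms shows that a birth has occurred. L385.00 stands beside separate codes for the same event in labour and delivery (L38A.00) and in the puerperium (L38B.00). Z243200 says that the first stage has not been reached.

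**5. Is this the list's general rule?** No. In the L11 to L13 blocks every entry is tied to delivery, labour or a postnatal complication, and none is antenatal. From L22 onward that restriction is not kept.

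**6. Own-birth terms.** At least six codes are lifelong attributes of the person coded: 63CE.00, 63CE.11, 63CE.12, 63CE.13, 63CE.14 and 63CF.00. Birth injuries such as Erb's palsy (Q206112) can also appear in later records. The 12 to 49 age limit removes such codes when they are dated in infancy. It does not remove them when they are recorded in an adult woman. Whether they are ever searched there is neither stated nor excluded.

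**7. Do the planned safeguards catch it?** A lone antenatal code conflicts with nothing, so conflict rules do not act on it. The Stage Four free-text search looks for evidence of pregnancy, which a truly pregnant but undelivered woman would have. The questionnaire to GPs asks only whether the mother and baby are correctly matched, not whether the outcome or date is right.

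**The case against.** The strongest reply is that the harm depends on an algorithm the Protocol does not show. A reader might infer that each such code generates a live-birth delivery dated to the day of the code, even in women who have not delivered or were never pregnant. The document does not support that:
- No section says that one code alone creates a delivery. The one-indication rule governs entry to the pregnancy register, not live-birth status.
- No section says that the code date becomes the delivery date. The list also holds six-week maternal examinations and infant-feeding codes at up to six months. These fit better with a broad set of supporting evidence from which a date is estimated. Turning an assumed gestation at coding into a shift in weeks is therefore not justified.
- No section says that baby codes are searched in mothers' records. Because a birth date for the baby is also estimated, those codes have an obvious use in the child's record. A false link would further need a child to be matched to the woman.

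It is also fair to say that some terms are weaker examples than they look. About a third of the 17 (6/17) describe labour or puerperal events. Elderly primigravida and grand multiparity fall under the heading for problems affecting labour (L29). L385.00 falls under anaesthetic complications of labour and delivery (L38). Finally, refining the link is a stated objective.

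All of this limits the claim about consequences. It does not explain why codes for an undelivered state are labelled as live birth, especially where a delivered version is already listed. Nor is this detail left to a later plan, since the Protocol itself sets out the list.

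**Conclusion.** The point holds as a fault in the list and a risk to classification, not as a demonstrated error in the linked data. Of the 17 antenatal-qualified codes on the live-birth list, 11 have a delivered version listed separately, and about 11 do not imply labour. At least five pregnancy-status codes add to these.

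On the assumption that listed codes count as live-birth evidence, as the heading says, they can generate live-birth classifications for ongoing or later-lost pregnancies, and delivery dates that are too early. How often cannot be computed, because neither code frequencies nor the dating algorithm is given.

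The own-birth terms carry the same risk only if they are searched in the records of women aged 12 to 49. The stronger reading, that never-pregnant women do generate deliveries, is not established.

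**What to change.** 1. Take the antenatal-qualified codes that do not imply labour, and the status codes, out of the live-birth list. These are about 11 of the 17, plus terms such as L295.00, L294.00, L227.00, L385.00 and Z243200. Keep them as evidence of pregnancy only, not of a live birth or its date. The delivered versions stay.
2. State that own-birth and neonatal codes are used only in the child's record.
3. Re-run the existing link with the revised list and report how many links are lost or re-dated. That supplies the size that cannot be computed now.

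The cost is a code-list review by the team that already updates the link monthly, and one re-run. The downside is some loss of sensitivity: a few true deliveries known only from a moved code would lose live-birth status until another record corroborates them.
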